### Sample size

2.12.

Power and sample size calculations were based on clinically meaningful differences between treatment groups with respect to changes in the outcomes across time (i.e. intervention effect). For the primary outcome - any SV/ARA perpetration at Time 3, the detectable difference between arms was calculated based on traditional methods that assumed a fixed number of clusters as well as fixed number of subjects per cluster [94]. Twenty-one clusters were randomized, assuming a within-cluster intra-class correlation (ICC) of 0.01 (within-school correlations for abuse perpetration, similar to our team’s prior work with a related sexual violence prevention program with male athletes [37,95]), and a 20% baseline SV perpetration rate in the control arm. With 866 participants (approximately 41 boys at each site) and an 80% retention rate at Time 3, we expect to have 80% power to detect an absolute difference in SV perpetration of 8.3 (42% relative decrease) due to the intervention. We anticipate having ample power to detect clinically meaningful changes in bystander behaviors and the secondary outcomes as well. Based on previous studies, the within-cluster ICCs for each of our secondary outcomes ranged from 0.006 to 0.01. If we assume the upper end of that range, we will have at least 80% power to detect standardized mean differences as small as 0.23 between study arms.

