### Statistical methods

2.18.

Generalized linear mixed models will be used to account for the correlation among youth from the same cluster as well as the correlation between observations from the same youth. Descriptive statistics will be used to summarize the sample with regard to baseline characteristics of interest. Means and standard deviations will be presented for continuous variables, while sample proportions will be provided for categorical variables. 95% confidence intervals will accompany all sample statistics. Primary assessment of intervention effects will be based on intent-to-treat estimates. As-treated, or treatment-on-the-treated (TOT), effect parameters will be estimated in secondary analyses and reported as exploratory. Between-site differences regarding intervention effects will be assessed based on level of staff/facilitator engagement in curricular delivery as well as other observed external factors that may interact with the intervention to alter outcomes. SAS software will be used for all statistical analyses.

To assess differences at baseline between the youth in the experimental and control groups, demographics such as grade-level, race, nativity, and parental education will be compared while accounting for within-neighborhood clustering. Demographic variables as well as neighborhood-level characteristics resulting in between-arm imbalances will be considered as covariates in the primary and secondary analyses.

Participation bias will be assessed by comparison of age and race/ethnicity of youth participating in the study compared to the overall demographics of adolescents (school district and census data). Significant differences detected via chi-square analysis will be noted as potential validity threats.

An attrition analysis will be conducted by comparing youth who completed follow-up surveys with those who did not with regard to demographics as well as outcomes measured at baseline. All hypotheses will be two-sided tests with a significance level of 5%.

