Missing data were minimized as much as possible by keeping the surveys as short as possible to reduce survey burden, encouraging youth to be as complete and honest as possible by ensuring anonymity of the surveys, and working assiduously with community partners to ensure that youth stay engaged and can be tracked to complete follow up surveys. Mechanisms for missing data will be investigated by comparing important covariates between youth with and without missing data at each time point. We will characterize these mechanisms as 1) missing completely at random (MCAR), 2) missing at random (MAR), or 3) not missing at random (NMAR). If the nature of our missing data is ignorable (either MCAR or MAR), our primary analysis will be sufficient given that it is a likelihood-based approach to handling missing data. Additionally, we will conduct various sensitivity analyses such as multiple imputation via chained equations (MICE) and complete-case analyses. If our missing data is non-ignorable (MCAR), we will investigate other methods such as joint or shared parameter models.

The primary outcome for this study is reductions in self-reported perpetration of SV and ARA at Time 3, compared to controls. We will examine whether Manhood 2.0 results in improvements in the primary outcome assessed at 9 months after end of program (Time 3) compared to controls. Generalized linear mixed models (GzLMM) will be used and will include variables for baseline SV/ARA perpetration, treatment group, and random effects for cluster. For the primary outcome and other binary outcomes, the GzLMMs will be fit using a logit link; for all other continuous outcomes, an identity link function will be used.

For positive bystander intervention and the remaining secondary outcomes, the models will include variables for the secondary outcome at baseline, treatment group, and random effects for cluster. This will allow us to assess the effect of the study arm after accounting for clustering within neighborhoods. As an exploratory analysis, all three time points will be included in a single generalized linear mixed model to quantify the long-term trajectories of each of the secondary outcomes.

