	**Secondary Outcomes: bystander behaviors, intentions to intervene, gender attitudes, recognition of abusive behavior, condom and contraceptive self-efficacy (differences between intervention and control at Time 2 and Time 3)**					
Positive bystander intervention behaviors [37]	I have not experienced this in the past 3 months. (0) I didn’t say anything. (−1) I told the person in public that acting like that was not okay. (+1) I laughed or went along with it (−1) I told the person in private that acting like that was not okay. (+1) I talked to an important adult about it privately (like youth leader, teacher, coach). (+1) Sum items with at least 1 positive response behavior (noted as +1) endorsed	X		X	X	*The following questions ask about specific behaviors that you may have seen or heard among your male peers or friends. If you experienced this at least once in the past 3 months, how did you respond?* 1. Making rude or disrespectful comments about a girl’s body, clothing, or make-up. 2. Spreading rumors about a girl’s sexual reputation, like saying “she’s easy.” 3. Telling sexual jokes that disrespect women and girls. 4. Bragging about what they and their girlfriend do sexually. 5. Showing other people sexual messages or naked/sexual pictures of a girl on a cell phone or the internet. 6. Doing unwelcome or uninvited things toward a girl (or group of girls) such as howling, whistling, or making sexual gestures. 7. Fighting with a girl where he’s starting to cuss at or threaten her. 8. Taking sexual advantage of a girl (like touching, kissing, having sex with) who is drunk. High from drugs, or passed out. 9. Shoving, grabbing, or otherwise physically hurting a girl.
Condom negotiation self-efficacy [86]	5 point Likert scale from ‘strongly disagree’ to ‘strongly agree,’ modeled as a mean score	X		X	X	1. I feel confident in my ability to discuss condom use with any partner I might have. 2. I feel confident in my ability to suggest using condoms with a new partner. 3. If I were to ask my partner to use a condom, I would be afraid that my partner would be upset with me. *(reverse coded)* 4. If I were unsure of my partner’s feelings about using condoms, I would not ask my partner to use one. *(reverse coded)* 5. If my partner didn’t want to use a condom during sex, I feel confident in my ability to refuse to have sex.

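### The main models for the secondary outcomes use one follow-up wave at a time, so the T3 contrast takes nothing from T2; one repeated-measures model would be a modest, cheap improvement.

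*Protocol article*

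**What the plan says.** All places are in the protocol article.

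- **Table 2, secondary outcomes.** All six outcomes are collected at T1, T2 and T3. The contrast is given as "differences between intervention and control at Time 2 and Time 3".
- **Statistical methods, secondary outcomes.** In the main analysis, "the models will include variables for the secondary outcome at baseline, treatment group, and random effects for cluster". No time term, arm-by-time term or youth-level term is listed.
- **Same paragraph, next step.** "As an exploratory analysis, all three time points will be included in a single generalized linear mixed model to quantify the long-term trajectories".
- **Statistical methods, opening sentence.** The mixed models are to account for clustering "as well as the correlation between observations from the same youth".
- **Statistical methods, missing data.** If data are missing at random, the primary analysis is held to be sufficient because it is likelihood-based. Multiple imputation by chained equations and complete-case analyses are added as sensitivity analyses.
- **Primary outcome section.** Perpetration is measured at baseline and T3 only.

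**The concern.** Two time-specific contrasts cannot be read from one model that has no time term. The listed terms therefore describe a baseline-adjusted model fitted to one follow-up wave. In such a model for T3, a youth without a T3 score has no outcome row, whatever was recorded at T2.

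Three things follow.

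1. The opening statement on within-youth correlation is met only in the exploratory model. For the secondary outcomes, where repeated follow-up exists, this matters.
2. If the likelihood argument is carried over to the secondary outcomes, it covers T3 only when loss is random given baseline and arm. A joint model also allows loss to depend on observed T2 scores.
3. The planned safeguards do not fill the gap. A complete-case analysis of T3 would largely repeat the single-wave model. The attrition analysis compares demographics and baseline outcomes, so it would not show loss linked to T2.

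At stake are some precision and, under particular patterns of loss, a small bias in the T3 contrasts of the secondary outcomes.

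**Working it through.** **1. The plan's own figure.** Inputs from Sample size: "With 866 participants (approximately 41 boys at each site) and an 80% retention rate at Time 3"; 21 clusters; "the within-cluster ICCs for each of our secondary outcomes ranged from 0.006 to 0.01", with the upper end used; 80% power for a standardized mean difference (SMD) of 0.23. Tests are two-sided at 5% (Statistical methods). The 11:10 allocation is treated as equal.

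Design effect = 1 + (m − 1) × ICC. Detectable SMD = (1.960 + 0.842) × √(2 / effective n per arm).

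- All 866: m = 866/21 = 41.24; design effect 1.402; effective n = 433/1.402 = 308.8; SMD 0.225; power at 0.23 is 81.5%.
- 80% retained (866 × 0.8 ≈ 693, about 173 lost): m = 32.99; design effect 1.320; effective n = 262.4; SMD 0.245; power at 0.23 is 75.0%.

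The stated 0.23 fits full enrolment but not 80% retention. That is a separate matter; here 0.245 is the starting value for T3.

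**2. Precision.** The article does not give the T2–T3 correlation given baseline (ρ) or the share of T3-lost youth seen at T2 (s). Assumed ranges: ρ 0.3 to 0.7 and s 25% to 75%, which is about 43 to 130 of the 173. Everyone with T3 is taken to have T2.

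- Youth-level factor, T3 only: 1/0.8 = 1.25.
- Youth-level factor, joint: (1 − ρ²)/0.8 + ρ²/(0.8 + 0.2s).
- With clustering: 0.01 + 0.99 × factor/41.24.

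Example, ρ = 0.5 and s = 50%: joint factor = 0.75/0.8 + 0.25/0.9 = 1.2153. The variances are 0.04001 (T3 only) and 0.03918 (joint), a ratio of 0.979, or 2.1% lower.

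| Retention | ρ | s | Variance ratio | Reduction |
|---|---|---|---|---|
| 80% | 0.3 | 25% | 0.996 | 0.4% |
| 80% | 0.5 | 50% | 0.979 | 2.1% |
| 80% | 0.7 | 75% | 0.942 | 5.8% |

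At 80% retention the detectable SMD falls from 0.245 to between 0.245 × √0.942 = 0.237 and 0.245 × √0.996 = 0.244. Power at 0.23 rises from 75.0% to between 75.2% and 77.5%. At an assumed 60% retention the variance reduction is 1% to 13%.

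**3. Bias.** Simulation under assumed values: correlation 0.5 of baseline with each follow-up and 0.6 between T2 and T3, 20% T3 loss, no true effect, 200,000 youth per arm, no cluster effect, Monte Carlo error about 0.003. The slope is the log-odds of T3 loss per SD of T2. Entries are bias in SD.

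| Slope in the two arms | T3 only | Joint, s = 50% | Joint, s = 25% |
|---|---|---|---|
| 0 vs −0.5 | 0.034 | 0.015 | 0.024 |
| +0.3 vs −0.5 | 0.059 | 0.029 | 0.038 |
| 0 vs −1 | 0.068 | 0.033 | 0.043 |

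The joint model keeps 44% to 49% of the bias at s = 50% (0.015/0.034 to 0.033/0.068) and 63% to 71% at s = 25% (0.043/0.068 to 0.024/0.034). Youth who miss both visits supply no T2 score, so the joint model cannot correct for them.

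In 1,500 simulated trials of 866 youth with only 15% random T2 loss, the T3-only bias was 0.033, 0.047 and 0.056, and the joint-model bias at most 0.003. That is a favourable case. With a slope of −0.5 in both arms, both models were off by about 0.001, which is nil.

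Against the plan's 0.23, the T3-only bias is 0.033/0.23 = 14% to 0.068/0.23 = 30%, in these scenarios only.

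**The case against.** Baseline-adjusted comparison at a fixed visit is a legitimate analysis and matches the form used for the primary outcome. The article never says that the T2 and T3 models are separate; its opening sentence on within-youth correlation points the other way, and covariance details usually sit in an analysis plan that is not shown. This stands in part: single-wave fitting is inferred from the listed terms. But the terms and the exploratory rank of the all-wave model are stated choices, and they do not fit the opening sentence.

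A reader might go further and infer any of the following. The documents do not support them.

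- **That youth lost after T2 are thrown away.** They stay in the T2 contrast and in the exploratory model, and can inform multiple imputation if T2 is included there. They are absent only from the T3 contrast.
- **That the T3 contrast is biased whenever loss is related to T2.** The arm difference is biased only if that dependence also differs by arm.
- **That the Discussion shows such loss.** It expects heavier loss among the most vulnerable and justice-involved youth, and plans analyses with and without the latter. It says nothing about a difference between arms or about T2 scores. The slopes above are assumptions.
- **That a joint model removes the bias.** It does so nearly completely only if most T3-lost youth were seen at T2. Hard-to-reach youth may miss both visits.

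**Conclusion.** The point holds as a limited improvement to the secondary analyses. As written, the main T3 contrasts use no T2 information, do not reflect the announced within-youth correlation, and support the missing-at-random argument only given baseline and arm.

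The sure gain is small: about 0.4% to 6% lower T3 variance at 80% retention, for ρ between 0.3 and 0.7 and 25% to 75% of T3-lost youth seen at T2. The possible further gain is removal of part or most of a 0.03 to 0.07 SD bias. It rests on T2-dependent loss that differs by arm, which is plausible in an unblinded trial but not shown. In the scenarios run, the joint model was never materially more biased than the T3-only model. The primary outcome is not affected.

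**What to change.** - Make one repeated-measures mixed model the main analysis of each secondary outcome: T2 and T3 as outcomes; arm, categorical time, arm-by-time, baseline score and baseline-by-time; a random cluster effect; and a within-youth covariance. Read the T2 and T3 arm differences from it.
- Keep the single-wave models as sensitivity analyses.
- Include T2 scores in the imputation model for T3.
- Where any single-wave T3 result is reported, limit the missing-at-random statement to loss given baseline and arm.

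The cost is wording and one covariance specification. No new data are needed, since the schedule already collects T2. The proposed model is not identical to the exploratory one, which is meant to describe trajectories over all three time points, so its terms have to be written out.

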### Experimental and control arms

2.5.

Program Delivery: Both experimental and control arm interventions involved 18 h of curriculum, generally spread out over 3 to 6 week periods. The program was delivered with some variation in schedules to meet the needs of community partners and participating youth. Such configurations included but were not limited to: three 6-h sessions spanning three weekdays during the summer (for job skills training only), nine 2-h sessions held twice per week on weekday evenings, and six 3-h sessions held once or twice per week on weekday evenings or Saturday afternoons (which was the preferred and most commonly used design).

Fidelity to intervention: For both intervention and control arms, research assistants were present at every session to track attendance, facilitate program implementation logistics (such as ordering food), and to complete detailed fidelity forms that assessed facilitators’ ability to deliver the content of the program as intended.

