Following Twisk and Proper’s recommendations for randomized controlled trials with both baseline and follow up measures (in this case abuse perpetration) [100], we will also construct multinomial logistic regression models that account for presence or absence of baseline perpetration. That is, we will examine intervention effects among youth reporting baseline SV/ARA perpetration and the likelihood of becoming ‘non abusive’ at follow up (i.e., an ‘early intervention’ effect). Similarly, we will examine intervention effects among youth with no baseline SV/ARA perpetration and the likelihood of ‘staying non abusive’ (i.e., a primary prevention effect). We have used this approach to analyze intervention effects on abuse exposure in our school health center relationship abuse prevention study [101].

We will also conduct two sets of exploratory analyses. First, we will conduct an intensity-adjusted analysis that reflects the actual delivery of the program. To achieve this, we will use a continuous score of “intensity” to replace the binary intervention variable in the models for the primary analysis. This score will be calculated for each round (program delivery) by using two sources of information. The first is information collected systematically about each session by trained research assistants who observed the sessions, including whether each task assigned to a module was performed (yes or no). The second is a summary measure of overall attendance for each round, tracked by using sign-in sheets with the research assistants. The second set will be a per-protocol analysis. This set of models will include only participants in the intervention arm that received the full intervention, defined as having covered a minimum threshold of tasks across the six sessions and having sufficient attendance. These measures replicate the intensity score values, but are then dichotomized to yes or no to receiving the full intervention. All control arm participants will be included in these models.

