The study also has several limitations. The surveys are collected anonymously with each participant creating their own personal identification code that only they will know to match surveys over time. Thus, the dosage of program received (i.e., proportion of program completed) can only be calculated at the level of each round rather than at the individual level. As a community-based study recruiting youth who are at high risk for school ‘push out,’ retention of this cohort remains a critical challenge, with the most vulnerable at especially high risk for being lost to follow up. Additionally, youth who are juvenile justice system-involved are particularly difficult to retain. Thus, we are likely to have significant missing data from rounds involving justice system-involved youth. We will conduct sensitivity analyses both with and without these youth in the sample to examine differences in intervention effects.

In summary, this study protocol is intended to evaluate Manhood 2.0 using a rigorous design to determine the effectiveness of a community-based sexual violence and adolescent relationship abuse prevention program for high school age youth living in low resource neighborhoods. Findings may provide urgently needed information about the effectiveness of a gender transformative program that combines healthy sexuality skills, gender norms change, and bystander skills to interrupt peers’ disrespectful and harmful behaviors to reduce SV/ARA perpetration among adolescent males.

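### The exploratory per-protocol analysis filters intervention rounds on delivery and attendance but keeps every control participant, so it is no longer a randomised comparison

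*Protocol article*

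**What the plan says.** Section 2.18 (Statistical methods) sets the hierarchy: "Primary assessment of intervention effects will be based on intent-to-treat estimates". It then adds that "As-treated, or treatment-on-the-treated (TOT), effect parameters will be estimated in secondary analyses and reported as exploratory", without saying at what level or by what estimator.

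Later in the same section: "We will also conduct two sets of exploratory analyses". The first replaces the treatment indicator with an intensity score computed for each round from observed task completion and overall attendance. The second is the per-protocol analysis. On the intervention side, "This set of models will include only participants in the intervention arm that received the full intervention", judged by a minimum of tasks covered and sufficient attendance. These are the same intensity measures, dichotomised. On the control side, "All control arm participants will be included in these models".

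Section 2.5 shows that the raw material exists in both arms: "For both intervention and control arms, research assistants were present at every session to track attendance", and they also completed fidelity forms. Section 2.17.1 says the surveys are anonymous and linked by a self-created code. The Discussion states the consequence as a limitation: programme dose "can only be calculated at the level of each round rather than at the individual level".

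**The concern.** Delivery and attendance arise after randomisation. Selecting on them in one arm only leaves well-delivered intervention rounds facing all control rounds, good and bad. Any feature that makes a round hard to deliver or poorly attended, and that also goes with perpetration, is removed from one side and kept on the other. The resulting contrast mixes programme effect with selection. Because the asymmetry is written into the plan, it is not a detail left for an analysis plan to settle.

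A link between delivery and risk is plausible here. Five of the 38 sites are juvenile-justice centres (Section 2.4.1), and the Discussion says the most vulnerable youth are the hardest to retain. That statement concerns follow-up surveys, however, so it suggests a link with session attendance and does not establish one.

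A smaller issue sits beside this. Section 2.18 offers as-treated and TOT as two names for one thing. As-treated compares youth by treatment received. TOT is the effect among those treated, usually estimated with randomisation as an instrument. They rest on different assumptions and need different data.

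**Working it through.** The plan gives no figure for this analysis, so there is none to reproduce. The size of the problem can only be shown as a range.

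**Inputs from the protocol article:** 20% control-arm perpetration, ICC 0.01, 80% retention at T3 and 21 clusters (Section 2.12); 464 and 402 enrolled (Results); two-sided 5% tests (Section 2.18).

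**Assumptions, not in the documents:** 20% true risk at T3 in both arms (no effect); a share q of intervention youth in excluded rounds; risk pe in those rounds; no baseline adjustment.

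**Formula.** Risk in kept intervention rounds: pk = (0.20 − q × pe)/(1 − q). Spurious benefit = 0.20 − pk, because all controls stay in at 20%.

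**Chance of a significant result.** Followed up: 866 × 0.80 = 692.8, or 33 per cluster. Design effect: 1 + (33 − 1) × 0.01 = 1.32. Effective control n: 402 × 0.80/1.32 = 244. Effective intervention n: 464 × 0.80/1.32 = 281, times (1 − q). A two-proportion normal test then gives the last column, which is approximate.

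| q | pe | pk | Spurious benefit | Chance of p < 0.05 |
|---|---|---|---|---|
| any | 20% | 20.0% | 0 points | 5% |
| 10% | 25% | (0.20 − 0.025)/0.90 = 19.4% | 0.6 points | 5.3% |
| 20% | 30% | (0.20 − 0.06)/0.80 = 17.5% | 2.5 points | 10.6% |
| 30% | 30% | (0.20 − 0.09)/0.70 = 15.7% | 4.3 points | 21% |
| 20% | 10% | (0.20 − 0.02)/0.80 = 22.5% | −2.5 points (apparent harm) | not computed |

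**Plausibility check.** The split between kept and excluded rounds contributes variance q(1 − q)(pe − pk)². If the ICC between rounds were the plan's 0.01, this could not exceed 0.01 × 0.20 × 0.80 = 0.0016. Since the spurious benefit equals q(pe − pk), it would be at most 0.04 × √(q/(1 − q)): 1.3 points at q = 10%, 2.0 at 20%, 2.6 at 30%. The 2.5-point row needs a between-round ICC of at least 0.2 × 0.8 × 0.125²/0.16 = 0.016, and the 4.3-point row 0.3 × 0.7 × 0.143²/0.16 = 0.027. The plan's 0.01 refers to clusters. Rounds may differ more than that, but the documents do not say.

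**TOT.** With no control youth receiving Manhood 2.0 (assumed), the Wald ratio is the ITT difference divided by the share treated. For the plan's 8.3-point difference and assumed shares of 0.9, 0.7 and 0.5: 8.3/0.9 = 9.2, 8.3/0.7 = 11.9, 8.3/0.5 = 16.6 points. No step needs an individual survey linked to an attendance record. It does require that arm assignment affects outcome only through receipt, and that attendance among followed-up youth resembles attendance overall.

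**The case against.** The strongest reply is that these analyses carry little weight. Both the per-protocol and the TOT results are labelled exploratory beside a primary intent-to-treat analysis. That stands. A reader might infer that the trial's main conclusion is at risk, or that a null primary result would be displaced by the per-protocol one; nothing in the plan supports either.

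Second, the bias is conditional. No passage says that poorly attended rounds hold higher-risk youth. The primary model adjusts for baseline perpetration, and the per-protocol models, if they keep that covariate, would absorb part of any pre-existing difference. The Discussion also plans sensitivity analyses with and without justice-involved youth. This stands as a limit on size and direction, but it does not restore a randomised comparison.

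Third, a symmetric threshold is not a cure. The curricula differ, and one schedule of three 6-hour sessions was used for job skills only, so similar thresholds may select different kinds of youth in the two arms. That also stands and has to be stated with the result.

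Fourth, a reader might infer from the anonymity limitation that the promised TOT effect cannot be computed, or that Sections 2.18 and the Discussion contradict each other. The documents do not support this. No participant-level TOT is promised, the score is defined per round, the limit is disclosed, and TOT needs only aggregate attendance. What remains is loose wording: a round-level rule phrased as if it selected participants, and two estimands treated as one.

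**Conclusion.** The concern holds in limited form. The plan's own rule compares a post-randomisation selected intervention arm with an unselected control arm, and the data for a symmetric rule were collected. Under the assumptions shown, the spurious benefit runs from 0 points when delivery is unrelated to risk to 4.3 points when 30% are excluded at 30% risk; it becomes spurious harm if the excluded rounds are lower-risk. These are unadjusted illustrations, and the two larger ones require more variation between rounds than the plan's cluster ICC of 0.01. It would go too far to say that the analysis must favour the intervention. It is exposed to bias of unknown size and direction. The primary intent-to-treat conclusion is not affected.

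On the second issue, only a participant-level as-treated analysis by dose is ruled out by the anonymous surveys. A TOT effect is estimable from arm- or round-level attendance.

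**What to change.** - Apply the same kind of task and attendance threshold to control rounds, using the fidelity forms and attendance records kept in both arms. Because session formats differ, express it in terms that carry across arms, such as the proportion of planned tasks delivered and of hours attended.
- Keep the baseline-perpetration covariate in these models.
- Describe the analysis as a round-level, non-randomised exploratory comparison, and replace the wording about participants who received the full intervention with wording about participants in qualifying rounds.
- State with the result that symmetry removes the bias only if exclusion relates to risk similarly in both arms, and report how many rounds and youth each arm loses.
- In Section 2.18, separate as-treated from TOT. Say that as-treated by individual dose is not possible. If TOT is kept, name the estimator (randomised arm as instrument for arm- or round-level receipt) and its assumptions.

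The cost is a change of wording and a small loss of precision from the dropped control rounds. No new data are needed and the primary analysis does not change.
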